## Safety Outcomes

In general, heart rate is monitored during the testing phase. If any problems occur (very fast heart rate or very low heart rate) we would recognize it and could react immediately. In case of any emergency, a doctor in the sports medicine would be available at all times. Additionally, a defibrillator is available in a distance of 20m from the test location. The study staff is equipped with a telephone for emergency cases. The Swiss Paraplegic Centre has its own emergency number if medical aid is required. Also blood pressure is measured regularly. After every test session the participant will be asked if he suffered from gastrointestinal or other side effects and if he thinks that he got placebo or caffeine before the test.

# STUDY DESIGN

## General study design and justification of design

Our study will be conducted in a placebo-controlled, double-blind and randomised study protocol. In total every subject visits the Sport Medicine for four times whereas every visit takes 2 hours expect for the first one where only 30min are needed. Every subject has to undergo three test sessions at the Institute of Sports Medicine in Nottwil. Before these three sessions the subject will visit the Institute of Sports Medicine in Nottwil for recruitment issues which involves study informed consent and a health questionnaire with specific questions about diseases and family health history including a measurement of blood glucose level.

Then at the screening, the subjects have to perform a maximal exercise test (ramp protocol at the arm crank ergometer) to measure maximal oxygen uptake, maximal heart rate and maximal power output. After a little break, subjects have to perform a familiarization trial at the arm crank ergometer (Angio V2, Lode, Groningen, Netherlands). They have to perform exactly the same test as they have to perform later in the two test sessions.

Minimum two days and maximum two weeks later the subjects visit the Sports Medicine Nottwil for the first test session. At first, they have to answer some specific questions about sleep, recent training, recent nutritional intake and the actual health condition. Afterwards, they have to lie down for a 10 min rest where after 9 min blood pressure will be measured. HRV will be measured during 5 min the supine position and 6 min in the sitting position by means of a heart rate monitor. Paced breathing (15x/min) [12] is mandatory and will be paced through a metronome. During the HRV measurement also tidal volume will be measured. As the first HRV measurement session is finished, a venous blood withdrawal will be taken to measure catecholamine concentrations. Then, when all these measurements are completed, a supplement (either caffeine or the placebo) will be ingested in gelatine capsules. After the ingestion of these capsules, the subject has a 40 min break where they can read something or just relax. During these 40 min physical activity or the ingestion of any nutrition is prohibited.

After these 40 min, the second HRV measurement starts. The process of this measurement is exactly the same as for the first HRV measurement. They lay down for a 10 min rest with blood pressure measurement after 9 min. Afterwards again a 5 min HRV measurement in supine position and a 6 min measurement in sitting position will be performed. Tidal volume is measured during this HRV measurement.

When this second HRV measurement session is finished, a second blood withdrawal has to be taken. That means, one hour after the ingestion of either placebo or caffeine, catecholamines are analysed for a second time. After blood sampling, the warm up can start. After the standardised warm up lactate concentration of the blood is analysed taking 10 µl of blood from the earlobe using a blood lactate analyser (Biosen, EKF diagnostic, Cardiff, Great Britain) for analysis. The subject will be asked to evaluate the warm up by rating of the perceived exertion (following the Borg scale from 6 to 20). Then the 3 min exercise test can start. During this test, respiratory parameters will be measured using a device to measure oxygen consumption (MetaMax 3B,Cortex Biophysik GmbH, Leipzig, Germany). Just after having finished these 3 min of exercising, for a second time lactate concentration will be measured and again they have to rate the exertion using the Borg scale (6 to 20).

After a short 5 min break the third HRV measurement starts. Again HRV will be measured during a 5 min time in supine position and a 6 min time in sitting position. Tidal volume will be measured during the whole HRV measurement. With this HRV measurement the first test session is finished and a second test session will be conducted at least more than two days later in a randomised order.

The first visit will take 30 min. The screening and familiarization trial will be finished in around 75 min. For the two test sessions the subject has to be at the Sports Medicine for about 90 min.

In the following chart, the two 90 min test sessions are visually displayed.

[figure not shown]

As we know from previous studies conducted with disabled subjects, the level of the lesion is one critical point. Therefore, we tried to include subjects with almost the same lesion level and sensory and motor complete lesion. This could help us to have more homogenous groups of different populations.

## Methods of minimising bias

### Randomisation

Randomisation will be assessed by lot. 50 % of all the subjects will first conduct the placebo trial and the other 50% first the caffeine trial. With which trial they start will be assigned by lot. So, there will be an “A” lot and a “B” lot and the fortune will decide whether they have the A or the B trial first. The test administrator only knows whether they have to ingest supplement A or supplement B but he does not know which supplement it is.

Applying a significance level of 0.05 and a power of 0.8 with a difference of 7.59 and a standard deviation of 10 Watt, we receive a total sample size of 9. With inclusion of a 10% drop-out rate we obtain a total sample size of 10 subjects per group. With the three different groups (able-bodied, paraplegic and tetraplegic subjects) we have in total 30 subjects and thus 120 visits overall.

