| Control Intervention (if applicable): | Placebo (mannitol) |
| Number of Participants with Rationale: | 30 participants in total (10 per each group of able-bodied, tetraplegic and paraplegic subjects): this study is a pilot study thus no power analysis was performed. |
| Study Duration: | 20 months |
| Study Schedule: | 01. May 2014: start of data collection  31. December 2015: end of data collection |
| Investigator(s): | [name]  Sports Medicine, Swiss Paraplegic Centre, [name], [contact], [contact] |
| Study Centre(s): | Single-center study: Swiss Paraplegic Centre Nottwil |
| Statistical Considerations: | For analysing the differences pre and post ingestion of caffeine within a subject, a Wilcoxon test will be used.  The correlation between HRV and performance under caffeine treatment will be evaluated with the Spearman’s rank correlation coefficient. |
| GCP Statement: | This study will be conducted in compliance with the protocol, the current version of the Declaration of Helsinki, the ICH-GCP or ISO EN 14155 (as far as applicable) as well as all national legal and regulatory requirements. |

study summary in local language can be provided here (German)

Die Herzfrequenzvariabilität (HRV) beschreibt die Varianz der Zeitintervalle zwischen den einzelnen Herzschlägen. Sie ist ein Parameter zur Bestimmung der Funktion des Sympathikus und Parasympathikus des autonomen Nervensystems. Diese beiden Komponenten haben antagonistische Aufgaben bei der Regulation der viszeralen Funktion des Körpers. Während der Sympathikus eine eher anregende Wirkung hat, hemmt der Parasympathikus.

Aus der Analyse der HRV resultieren zwei Komponenten, welche den zwei Systemen zugeordnet werden können. Die low frequency (LF) repräsentiert den Sympathikus während die high frequency (HF) dem Parasympathikus zugeordnet wird.

Je mehr also zum Beispiel der Sympathikus aktiviert ist, desto grösser ist der Anteil des LF- im Vergleich zur HF-Komponente. Mit der Analyse der HRV lassen sich so Aussagen über die sympathische-parasympathische Balance machen.

Bei querschnittgelähmten Personen ist durch die Verletzung des Rückenmarks auch das autonome Nervensystem betroffen. Davon ist, aufgrund seiner Austritthöhe entlang der Wirbelsäule bis ca. zum 6. Brustwirbel, nur der sympathische Anteil betroffen. Der Parasympathikus dagegen tritt auf Hirnstamm-Höhe aus und ist so nicht direkt von der Unterbrechung der Rückenmarks betroffen.

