## Study Drug / Medical Device Accountability

The pharmacy of the Swiss Paraplegic Centre in Nottwil will produce the gelatine capsules filled with either caffeine or mannitol. They will put the expiry date on the packing. A pharmacist will then control the capsules and mark it as an “A” or “B” supplement for the blinding process. The pharmacy will produce enough capsules for the whole study. They will deliver us with 120 capsules of 100 mg and 60 capsules of 50 mg for each supplement (A or B). We calculated an average weight of 80 kg per subjects which means a dosage of 480 mg. Therefore we need for each subject 4x100 mg and 2x50 mg (30x4 100 mg=120 capsules; 30x2 50 mg=60 capsules).

Therefore we don`t have to worry a lack of capsules.

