## Determination of Sample Size

This study represents a pilot study and therefore no power analysis was performed.

A total of 36 subjects who are classified into 3 groups (tetraplegic, paraplegic, able-bodied) will be included which includes an over-recruitment by approximately 20% to take into account possible drop-outs. A minimum of 10 data sets will be required for each subject group.

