### Primary Analysis

For testing the first hypothesis

H_0_: m_1_ = m_2_ versus
H_1_: m_1_ ≠ m_2_
where m_1_ = performance (power output) under placebo
 m_2_ = performance (power output) under caffeine

the Wilcoxon signed-rank test will be used to compare the performance under placebo with that under caffeine for three subject groups separately.

For testing the second hypothesis

H_0_: m_1_ = m_2_ versus
H_1_: m_1_ ≠ m_2_where m_1_ = change in HRV from baseline to post-treatment under placebo treatment
 m_2_ = change in HRV from baseline to post-treatment under caffeine treatment

the Wilcoxon signed-rank test will be used to compare the performance under placebo with that under caffeine for three subject groups separately.

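### The power calculation in section 6.2.1 cannot be reproduced from its printed inputs, and the protocol elsewhere denies having one and gives a different recruitment total (36, not 30)

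*Protocol*

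**What the plan says.** The protocol speaks about sample size in several places.

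- **Section 6.2.1 (Randomisation)** reports a calculation. "Applying a significance level of 0.05 and a power of 0.8", it continues "with a difference of 7.59 and a standard deviation of 10 Watt, we receive a total sample size of 9". It then adds drop-out: "With inclusion of a 10% drop-out rate we obtain a total sample size of 10 subjects per group". Three groups give 30 subjects.
- **Synopsis (Number of Participants with Rationale)** plans "30 participants in total (10 per each group of able-bodied, tetraplegic and paraplegic subjects") and says that, as a pilot, the study had no power analysis. Section 3.8 also describes 30 subjects, and the capsule order in section 8.8 is worked out for 30.
- **Section 11.2 (Determination of Sample Size)** states "This study represents a pilot study and therefore no power analysis was performed". It then plans "A total of 36 subjects who are classified into 3 groups", a figure that includes over-recruitment of about 20%, and requires at least 10 data sets per group. Section 11.4.1 repeats the minimum of 10.
- **Sections 11.1 and 11.4.2** fix the test that any calculation should match. The alternative is two-sided, and "the Wilcoxon signed-rank test will be used to compare the performance under placebo with that under caffeine for three subject groups separately".

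**The concern.** Power output in the 3-minute test is one of the two primary outcomes. Section 6.2.1 is the only place that says what size of effect on it the trial can detect. Taken at face value, it tells an ethics committee or a later reader that each group of 10 has about 80% power for a 7.59 W difference. If that does not follow from the inputs, a non-significant result in one group could be given more weight than it deserves.

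The conflicting statements matter separately. A reader cannot tell whether a calculation underlies the sample size, or whether 30 or 36 people are to be recruited.

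**Working it through.** **Inputs.** Alpha 0.05, power 0.80, difference 7.59 W and SD 10 W (section 6.2.1); two-sided alternative (section 11.1); paired signed-rank test within each group (section 11.4.2). The type of SD and the within-subject correlation ρ are not stated, so both readings are worked through. Paired-t power comes from the noncentral t distribution with n − 1 degrees of freedom and noncentrality d√n, where d is the difference divided by the SD of differences. Signed-rank power is simulated with the exact critical value and normally distributed differences.

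**Step 1: try to reproduce 9, with 10 W as the SD of differences.** Then d = 7.59 / 10 = 0.759.

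- Normal approximation: n = ((1.960 + 0.842) / 0.759)² = 13.6, so 14.
- Other sample sizes:

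| n per group | Paired t | Signed-rank |
| --- | --- | --- |
| 9 | 52% | 45% |
| 10 | 57% | 55–56% |
| 15 | 78% | 76% |
| 16 | 81% | 78% |
| 17 | 84% | 81% |

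The requirement is therefore 16 (paired t) or about 17 (signed-rank). A one-sided test, which would contradict section 11.1, still needs 13 by paired t and gives 67% at n = 9. With 10 completers, 80% power needs d of about 1.00 (paired t) or 1.02 (signed-rank), that is, a difference of about 10 W.

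**Step 2: try to reproduce 9, with 10 W as a per-session SD.** The SD of differences is 10 × √(2(1 − ρ)).

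| ρ | SD of differences (W) | n for 80% (paired t) | Power at n = 9 (paired t) | Power at n = 10 (paired t) |
| --- | --- | --- | --- | --- |
| 0 | 14.14 | 30 | 29% | 33% |
| 0.5 | 10.00 | 16 | 52% | 57% |
| 0.7 | 7.75 | 11 | 73% | 79% |
| 0.75 | 7.07 | 9 | 80% | 85% |
| 0.8 | 6.32 | 8 | 88% | 92% |

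Power of 80% at n = 9 needs d = 1.067, so an SD of differences of 7.59 / 1.067 = 7.11 W and ρ = 1 − 7.11² / 200 = 0.75. This reading returns the protocol's 9 for the paired t-test. With the planned signed-rank test at ρ = 0.75, power is about 75% at n = 9 and 84% at n = 10.

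**Step 3: the totals.**

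- Section 6.2.1: 9 / 0.9 = 10 per group, and 3 × 10 = 30. The drop-out allowance is already inside the 30, and 9 completers per group are expected.
- Section 11.2: 3 × 10 completers = 30, and 30 × 1.2 = 36. The allowance is on top of the 30, and 10 completers per group are required.

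Each sum is right by itself. They differ in completers (9 or 10), drop-out allowance (10% or about 20%) and total (30 or 36).

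**The case against.** A reader might infer from Step 1 that 9 is simply wrong and that 16 are needed. The protocol does not support that. It never says that 10 W is the SD of differences, and a per-session SD with a correlation near 0.75 returns 9 by paired t-test. On that reading the 10 completers required by section 11.2 exceed 80% power even with the signed-rank test. This stands, and it limits the point to a calculation that cannot be reproduced as printed. It does not rescue the figure, because the protocol states no correlation, and paired-t power at n = 10 moves from 57% to 92% as ρ goes from 0.5 to 0.8.

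A reader might also infer a capsule shortage, since section 8.8 orders for 30 subjects and section 11.2 recruits 36. Section 8.1.3 provides for re-supply from the pharmacy, so no shortage follows. The order shows only that planning there used 30.

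It is also fair to say that the study is called a pilot throughout, that the statistical section itself makes no power claim, and that section 11.5 replaces drop-outs, so at least 10 data sets per group are to be analysed under either total. This lowers the practical risk. It does not remove the contradiction over whether a power analysis was done, or over how many people are to be enrolled.

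**Conclusion.** The point holds as a should-fix correction, in three parts.

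1. **The stated power is not reproducible.** With 10 completers per group and a 7.59 W difference, paired-t power is 57% if 10 W is the SD of differences. If 10 W is a per-session SD, it is 57%, 79%, 85% or 92% at correlations of 0.5, 0.7, 0.75 or 0.8. These figures assume normally distributed differences and a two-sided 0.05 test. The correlations are illustrative, since the protocol gives none.
2. **The protocol both reports and denies a power analysis.** This needs no assumption.
3. **The planned numbers conflict:** 30 or 36 recruited, 10% or about 20% for drop-out, 9 or 10 completers per group. This needs no assumption either.

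Confidence is high for the two contradictions and for the missing inputs. The documents do not show that 9 is definitely the wrong number.

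**What to change.** Choose one of two courses for the calculation:

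- delete it from section 6.2.1 and keep the pilot statement in the synopsis and section 11.2; or
- move it to section 11.2, say whether 10 W is a per-session SD or an SD of differences, state the correlation and that the test is two-sided, and restate the power of 10 completers for the signed-rank test, as a range if the correlation is unknown. The statements that no power analysis was performed must then go.

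In either case, use one recruitment total, one drop-out allowance and one number of completers per group in the synopsis and sections 3.8, 6.2.1, 8.8 and 11.2.

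The cost is protocol wording. The test, the hypotheses and the minimum of 10 data sets per group stay as they are, and no extra enrolment is asked for. The price is that the stated power may become less favourable, or be withdrawn.

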### Blinding procedures

The pharmacist will define which capsules contain caffeine and which mannitol. He will name it A or B supplement. The test administrator then just see the A or B capsules and delivers the right capsule at the test day to the subject.

The real classification of the A or B supplement to caffeine or placebo will be written on a paper in an envelope by the pharmacist and will not be open before the end of the analysis of the data.

Therefore, the study will be double-blinded as neither the participant nor the test administrator and the principal investigator know which supplement the subject has ingested.

### Other methods of minimising bias

After the recruitment visit the subjects will visit the Institute of Sports Medicine in Nottwil performing the 3 min performance test for familiarization purposes.

## Unblinding Procedures (Code break)

The code for the blinding will be stored in a sealed envelope at the principal investigators office. Just the principal investigator or the physician are allowed to open this envelope in case of an adverse event. Otherwise this envelope will be opened after termination of the statistical analysis of the data.

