### Storage Conditions

The capsules are stored in two different boxes. One box with the “A” supplement and the other box with the “B” supplement (either caffeine or placebo). They are stored at room temperature and not exposed to light. There is only limited access to the storage area, where only study personal will have a key.

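### A single study-wide A/B key, which may be opened for any adverse event, decodes every participant's sessions for whoever learns it; sections 6.2.2 and 6.3 also conflict on when it may be opened.

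*Protocol*

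**What the plan says.** **One code for the whole trial.** Protocol section 6.2.2 says: "The pharmacist will define which capsules contain caffeine and which mannitol. He will name it A or B supplement". Section 8.8 describes bulk delivery by letter, with quantities worked out for 30 subjects. Section 8.1.4 adds: "The capsules are stored in two different boxes", one for each letter. No participant-level code is described.

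**Staff know the letter.** Section 6.2.1 says: "The test administrator only knows whether they have to ingest supplement A or supplement B but he does not know which supplement it is". Section 7.3 repeats this.

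**One key.** Section 6.2.2 says: "The real classification of the A or B supplement to caffeine or placebo will be written on a paper in an envelope by the pharmacist". Section 6.3 places it: "The code for the blinding will be stored in a sealed envelope at the principal investigators office".

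**When it may be opened.** Section 6.3 says: "Just the principal investigator or the physician are allowed to open this envelope in case of an adverse event". It sets no limit on the kind of event. Section 6.2.2 says without exception that the envelope stays closed until the data have been analysed, and it lists the principal investigator among those who do not know the supplement. Section 10.1.1 notes that unblinding is needed to determine a SUSAR.

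**Clues collected by staff.** Heart rate is monitored during testing (5.4). Tolerance is asked 45 min after ingestion (9.2.4). After each session the participant is asked "if he thinks that he got placebo or caffeine before the test" (5.4).

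**The concern.** Emergency unblinding should cost the trial the blinding of one participant. With a shared letter, the answer for one participant is the answer for all. The wording in 6.3 allows this for any adverse event, and section 3.7 names headache, tremor, nausea and a higher heart rate as possible effects of caffeine. One of the two roles allowed to open the envelope is the principal investigator, who also has it in the office and whom 6.2.2 declares blinded. Nothing says how blinding is kept for the remaining participants afterwards.

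The shared letter also lets impressions from one participant inform the next. A suspicion that A is caffeine, formed in early sessions, applies unchanged to every later one.

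At stake is mainly power output in the 3-min all-out test, a primary outcome, and the verbally given rating of perceived exertion. Both can respond to expectation and to how staff encourage the participant. HRV is device-recorded under metronome-paced breathing and catecholamines are assayed in a laboratory, so they are less exposed.

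**Working it through.** **1. The two sections side by side**

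| Question | Section 6.2.2 | Section 6.3 |
| --- | --- | --- |
| May the key be opened before the analysis ends? | No; no exception given | Yes, for an adverse event |
| Is the principal investigator blind? | Yes | May open the envelope, which is kept in that office |

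Both statements about timing cannot hold as written.

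**2. Scope of one opening**

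Inputs: 30 participants (synopsis and 6.2.1) or 36 (11.2, with over-recruitment). Each has 2 test sessions, one with each supplement (9.3).

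- Shared code: 30 × 2 = 60 sessions, or 36 × 2 = 72.
- Code per participant: 1 × 2 = 2 sessions.

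The exposure is therefore 30 to 36 times larger. This count follows from the design alone and needs no assumption. It is an upper limit, for three reasons:

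- The key gives the meaning of a letter, and does not give an order that has not yet been drawn by lot.
- Sessions completed before the opening were conducted blind. What changes for them is only that their A/B labels can be read at analysis.
- The key reaches only the person who opens the envelope and anyone that person tells.

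**3. Accumulation of clues (illustration only)**

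Assume that each participant's reaction or guess points to the correct letter with probability p, independently, and that someone tallies the results by letter. The documents give no value for p. After 10 participants, with ties split evenly, the probability that the majority names the caffeine letter is

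P = Σ (k = 6 to 10) C(10,k) p^k (1−p)^(10−k) + ½ · C(10,5) p^5 (1−p)^5.

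For p = 0.60 the sum is 0.633 and the tie probability is 252 × 0.24^5 = 0.201, so P = 0.633 + 0.100 = 0.733.

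| Assumed p | P after 10 participants |
| --- | --- |
| 0.50 | 0.50 |
| 0.55 | 0.62 |
| 0.60 | 0.73 |
| 0.70 | 0.90 |
| 0.80 | 0.98 |

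With no information in the clues (p = 0.50) nothing accumulates. With even modest information it does, and only because the letter is common to all participants.

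**4. Timing of the clues**

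The participant's guess is taken after the session, so it cannot affect that session's test. It matters only if carried forward to later sessions. The tolerance question at 45 min comes before the all-out test, which is planned one hour after ingestion, so it can inform staff in the same session.

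**The case against.** Four objections deserve weight.

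*Opening is permitted, not required.* Section 3.2 does not expect side effects at the chosen dose, withdrawal for side effects (7.4, 8.3) needs no unblinding, and the only stated need is a SUSAR determination. The probability of an opening may be small, and the documents give no basis for estimating it. This stands: the point concerns the damage if an opening occurs and the absence of any text that limits it.

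*An opening does not unblind the trial as a whole.* A reader might infer that everyone becomes unblinded and that future allocations become predictable. The documents do not support that. Nothing in 6.3 passes the result to the test administrator or to participants, and the physician could open the envelope without the principal investigator learning the key. Order is drawn by lot, and the key does not disclose a lot not yet drawn. Everyone takes both supplements, so the key cannot steer anyone towards or away from caffeine.

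*The guessing figures rest on an assumption.* Accuracy could be low: section 3.2 mentions non-responders, and section 3.4 cites a study in which catecholamines did not rise in tetraplegic subjects. This also stands, so the table includes 0.50 and 0.55 and serves as illustration only.

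*This is a small pilot, and one of its two primary outcomes is device-recorded.* That narrows the concern to power output and perceived exertion but does not remove it.

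**Conclusion.** The point holds as a weakness of the blinding scheme that is cheap to repair, together with a contradiction that must be resolved. Sections 6.2.2 and 6.3 disagree on whether the key may be opened before the analysis ends, and the right to open it sits badly with the principal investigator's stated blindness.

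One opening gives the person who learns the key the meaning of the letter for 30 to 36 participants, up to 60 to 72 sessions, where a participant-level code would expose 1 participant and 2 sessions. From then on, later sessions and the A/B-labelled analysis are not blind to that person. It would be wrong to read 60 to 72 as a number of biased sessions, or to conclude that staff will work out the code: the first is a ceiling, and the second depends on an unknown guess accuracy. The code-break argument does not rely on the guessing figures.

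**What to change.** - Replace the communal A and B boxes with vials that the pharmacy fills per participant and session, labelled only with study ID and session 1 or 2, following a sequence list held by the pharmacy.
- Provide one sealed code-break envelope per participant, held by the pharmacy or the physician and not by the principal investigator. Emergency unblinding stays available, limited to the affected participant.
- Reconcile 6.2.2 with 6.3 on when a code may be opened and on the principal investigator's blinding, and align 6.2.1, 7.3, 8.1.4 and 8.8 with the new scheme.

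Cost: the pharmacy fills and labels 60 to 72 vials once body mass is known, keeps the sequence list and prepares 30 to 36 envelopes. That changes the dispensing workflow, since bulk supply by letter and allocation by A/B lot are replaced. It needs no extra staff, participant procedures, visits or sample size. One limit remains: because each participant takes both supplements, identifying one of his sessions still identifies the other, but it no longer says anything about anyone else.
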